## Abstract

**Background:**

Enhancing resiliency and optimizing readiness in military personnel is a high priority for the U.S. Department of Defense. Most military resiliency-enhancement programs are evidence-informed interventions. However, few randomized studies have demonstrated efficacy of any intervention or training program to enhance resiliency and prevent the development of psychological health symptoms in military personnel when exposed to operational stressors. This manuscript provides an overview of the theoretical foundation, research design, and research methods of a preventive intervention trial designed to evaluate the efficacy of a training program to enhance resiliency and prevent psychological health symptoms in military personnel. The resiliency training intervention is based on Acceptance and Commitment Therapy (ACT), an evidence-based intervention with broad empirical support for improving functioning in those living with psychological and medical conditions.

**Method/design:**

This study will evaluate the efficacy of a two-day training program based on ACT for fostering psychological flexibility, the central target in ACT, for enhancing resiliency, and for preventing the development of psychological health symptoms. The research participants will be a non-clinical population of active duty military personnel (*N* = 600). The ACT-based training program (*n* = 300) will be compared to a military resiliency training as usual, known as Master Resilience Training (*n* = 300). Assessment measures will be administered at the baseline assessment, after training, prior to a military deployment, and after returning from a deployment. Qualitative interviews will be conducted to provide feedback on the training program.

**Clinical Trial Registration:** NCT05094115.

## Introduction

1

Maintaining health, optimizing performance, and enhancing resiliency to occupational stressors in military personnel who are frequently exposed to austere environments and trauma is a significant challenge. The Department of Defense has invested significant resources to develop and evaluate programs to enhance resiliency, optimize operational readiness, and prevent deployment-related psychological health casualties in military personnel (1). A limited amount of previous literature has shown positive effects of self-reflection on the subsequent development of mental health symptoms in Australian military cadets (2, 3) and on posttraumatic stress symptoms following a debriefing intervention among recently deployed U.S. soldiers (4). These studies highlight the importance of using a valid control group, as well as the importance of implementing interventions to prevent or mitigate the development of psychological health symptoms in military personnel when exposed to occupational or operational stressors. Most military resiliency-enhancement programs, such as the U.S. Army’s Comprehensive Soldier Fitness Program, are evidence-informed interventions that are implemented as population health programs (5, 6). Indeed, the effectiveness of the Comprehensive Soldier Fitness Program, which is the Army’s current resiliency-enhancement program of record, has not been supported based on the results of controlled trials (7).

There are several reasons for the lack of rigorous (i.e., prospective, randomized controlled) resiliency-enhancement trials in U.S. military populations. First, scientifically evaluating the potential efficacy of a resiliency-enhancement training program requires a prospective study in which military personnel are randomized to different arms of a controlled intervention trial, which can be difficult in the contemporary operating environment. Second, various groups of military personnel might be ideal populations to study, but with each presenting with unique challenges. For example, one population might be new military recruits who are enrolled, randomized, trained, and evaluated as they complete basic military training, a demanding and highly stressful environment (8). Another population might be military special forces trainees who are about to start a training program, such as the U.S. Navy’s Basic Underwater Demolition/Sea, Air, and Land Teams (SEALs) course, which has been found to have a washout or dropout rate of about 80% (9, 10). Such intense training programs would provide a proxy for a high-stress environment that might be encountered during a deployment. However, most military trainees are considered protected populations, and their training programs are part of established training curricula that require high levels of military coordination and approval to modify for the purpose of conducting research. A final group who might be ideal to study are individuals who are scheduled to deploy to a high-risk/high-threat environment. However, designing and obtaining research regulatory review approval for a prospective study such as this would be extremely difficult, especially with the discontinuation of U.S. military combat deployments in support of Operation Iraqi Freedom in 2010 and Operation Enduring Freedom in 2014 (11). A rigorous schedule of deployment preparation activities makes adding something such as supplemental resilience training a challenge.

The current manuscript is a description of the methods for a research project funded through the U.S. Department of Defense’s Military Operational Medicine Research Program’s Resilience and Readiness Optimization/Enhancement (R2OE) Translational Research Award (W81XWH1910628; PI: [name]). The aim of the project is to conduct a randomized controlled trial evaluating the efficacy of psychological flexibility training based on Acceptance and Commitment Training to enhance resiliency in military personnel.

### Acceptance and commitment therapy and acceptance and commitment training

1.1

Acceptance and Commitment Therapy (ACT; pronounced as one word) is a contemporary, evidence-based, cognitive-behavioral approach that was originally developed to improve psychological health and functioning in those experiencing psychological health challenges (12, 13). It is also a promising psychological approach for resilience enhancement in adults (14, 15). We recently described the potential of this model for fostering resilience enhancement in military personnel (16). The present grant was funded to adapt and evaluate a military-relevant psychological flexibility training intervention based on ACT to enhance resilience and optimize readiness.

There are over 1,000 published randomized controlled trials (RCTs) of ACT for improving a broad range of biopsychosocial outcomes. These RCTs span applications of ACT for depression, anxiety disorders, substance use disorders, psychosis, tobacco use, eating disorders, general well-being, and a range of medical challenges (17–24). ACT has been found to optimize functional outcomes in diverse domains including improving workplace performance under stressful conditions, completing physical exercise regimens, improving parenting skills, and adhering to dietary restrictions (15). Moreover, ACT has been found to be efficacious when delivered by individuals from different professional disciplines and in a broad range of formats including individual and group psychotherapy, brief training workshops, and online delivery. This underscores the robustness of the model and the potential for scalability (25–28). When used in a training context, ACT may be referred to as Acceptance and Commitment Training.

In ACT, the broad goal is to help individuals identify and act consistently with their personal values and goals and to align their actions with those values even if they are experiencing psychological or physical discomfort (9, 10). According to the ACT model, suffering and impairment are primarily the consequence of psychological inflexibility (i.e., inability to persist in or change behavior according to situational or contextual factors and personally chosen values due to problematic, inflexible reactions to negatively evaluated internal experiences). Psychological inflexibility may be particularly detrimental when an individual is confronted with stress or adversity (12, 13). ACT also incorporates mindfulness as a method for increasing awareness of and for promoting a nonjudgmental stance toward unwanted internal experiences, as these are key elements of fostering psychological flexibility (12). Interventions targeting increased psychological flexibility—ACT being the foremost in this field—are recommended not only for facilitating recovery after stressors but also for enhancing resilience (14, 16, 29, 30). The psychological flexibility model aligns well with the flexibility sequence model, arguably the most thoroughly researched and well supported model of the resilience process across numerous populations (31).

## Materials and methods

2

### Institutional review board

2.1

This project has been reviewed and approved by the Institutional Review Board (IRB) at the University of Texas Health Science Center at San Antonio (UTHSCSA; 20210486HU) as the IRB of record. The University of Pittsburgh deferred its review to UTHSCSA as part of a single IRB authorization agreement.

### Design

2.2

The present RCT (*N* = 600) was designed to evaluate the efficacy of a novel, military-relevant, ACT-based resilience training that we refer to as Psychological Flexibility Training and that we developed for this project. The primary goal of this intervention is to enhance resiliency and optimize readiness in military personnel. For the proposed study, it is hypothesized that the ACT principles will also improve the psychological health outcomes by reducing symptoms of anxiety, depression, and posttraumatic stress disorder (PTSD) in military operational settings, as suggested by the Cochrane Database of Systematic Reviews on Psychological Interventions for Resilience Enhancement in Adults (14). We have two primary research hypotheses. First, we hypothesize that military personnel who receive psychological flexibility training will demonstrate a statistically significant increase in psychological resiliency compared to military personnel receiving training as usual over the course of the study. Second, we hypothesize that military personnel who receive Psychological Flexibility Training will demonstrate a statistically significant increase in psychological resiliency after completing a military operational deployment compared to a group of military personnel receiving military resilience training as usual. Military training as usual for the Army is Master Resilience Training, which is the resilience enhancement component of the broader Comprehensive Soldier Fitness Initiative (32). Of note, all participants receive Master Resilience Training as part of their training as usual. Thus, the current study is testing the incremental value of adding Psychological Flexibility Training.

#### Randomization

2.2.1

Recruited personnel will be randomized as a group to Resilience Enhancement through Acceptance and Commitment Training (REACT) or regular programming. Group randomization will be completed prior to recruitment or consent. Groups will be randomized by a randomization list generated by the research team’s Biostatistics Core. The randomization list will use random blocks of 4, 6, and 8 to ensure roughly equal numbers of groups in each condition as the study progresses and to reduce the anticipation of group assignment and thereby the potential for bias.

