#### Source of population

2.3.1

Active duty U.S. Army soldiers assigned to Fort Cavazos (formerly Fort Hood), Texas, will be eligible to participate in the R2OE study. One unit that has already agreed to participate representing a military unit regularly scheduled to deploy to high-risk/high-threat environments is the 3rd Security Force Assistance Brigade (SFAB). SFABs are specialized Army units formed to train, advise, assist, enable, and accompany operations with allied and partner nations. They were created with the intent to reduce the burden of such operations on conventionally organized Brigade Combat Teams (BCTs), allowing BCTs to focus on fighting near-peer threats. Designed on the model of a standard infantry BCT, SFABs are composed of approximately 800 experienced senior personnel, primarily commissioned, warrant, and non-commissioned officers. They are selected from regular Army units and given additional training at the Military Advisor Training Academy at Fort Moore, Georgia. We will begin recruitment efforts with the 3rd SFAB. Should recruitment from SFABs prove insufficient, we will recruit from additional units stationed at Fort Cavazos, such as Brigade Combat Teams and other units that most closely resemble the SFABs in terms of military service characteristics.

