### Recruitment & randomization

2.4

Soldiers are recruited through briefings at various unit meetings as well as at the unit’s Newcomers’ Briefing held monthly. Any soldier, 18 years or older, is eligible for inclusion. There are no exclusion criteria. Participants are equally randomized between the two groups stratifying for rank to ensure equal numbers of junior non-commissioned officers (NCOs; grades E-4 to E-6), senior NCOs (grades E-7 to E-9), and officers (warrant and commissioned) are in each group. In accordance with Department of Defense (DoD) Instruction 3216.02, participants can be compensated if study participation does not adversely impact their ability to perform their assigned duties. Five assessments are scheduled. Each time an assessment is completed, $25 can be compensated, for a total of $125.

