#### Power analysis

2.7.1

Statistical power estimates were obtained from the PASS15 software (NCSS, 2017) modules for comparison of two means or two proportions in a cluster randomized design. Estimates were obtained for a range of standardized mean differences (Cohen’s *d*) from 0.35 to 0.50, which range from modest (*d* = 0.35) to medium in size (*d* = 0.50). Effect sizes below 0.35 are unlikely to be clinically significant and *d* = 0.50 is often considered to be a threshold for a meaningful difference. We also estimated the reduction in Failure % that was detectable at 0.80 assuming a base rate of 80%. We specified a total of 12 clusters of 50 participants for a total *N* = 600. The proposed sample size (*N* = 600) provides statistical power of at least 80% to detect a standardized mean difference (or change over time) in the “small to moderate” range (Cohen’s *d* of 0.30). This applies not only to analyses involving the entire randomized sample but also for analyses based on subsamples based on factors such as deployment, demographics, or other military service characteristics.

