#### Addressing hypotheses

2.7.2

The first research question relates to the pre-post training effect of workshop participation. Analyses will be based on changes during the 4 months before and following the training and will analyze data from all randomized participants. The second research question relates to the effect of training on change during deployments. Analyses will use data only from deployed participants. As deployments occur at varied points in time and are variable in duration, the selection of the baseline and post-deployment assessments for these analyses will be based on the deployment dates of each participant.

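### Primary hypothesis 2 uses only deployed soldiers, but the group randomization does not balance the arms on scheduled deployment

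*Protocol article*

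**What the plan says.** The protocol article, section 2.2.1 (Randomization), allocates clusters: "Recruited personnel will be randomized as a group". It adds that "Group randomization will be completed prior to recruitment or consent". The only balancing device given there is the blocked list: "The randomization list will use random blocks of 4, 6, and 8 to ensure roughly equal numbers of groups in each condition".

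Section 2.4 (Recruitment & randomization) names the only stratification factor in the article, and words it for individuals: "Participants are equally randomized between the two groups stratifying for rank".

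Section 2.7.1 (Power analysis) sizes the trial as a cluster design: "We specified a total of 12 clusters of 50 participants". It extends its power statement to subsamples defined by deployment.

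Section 2.2 (Design) states two primary hypotheses, the second on resiliency after a deployment. For that one, section 2.7.2 (Addressing hypotheses) restricts the data: "Analyses will use data only from deployed participants". It also says that deployments differ in timing and length and that each participant's own dates select the assessments. Section 2.3.1 describes the first brigade as "a military unit regularly scheduled to deploy to high-risk/high-threat environments". In section 2.7, deployment history enters the models as a covariate. It is not part of the allocation.

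**The concern.** Blocking over all groups keeps the overall count near 6:6. It does not balance a subset of those groups. The clusters that supply the data for hypothesis 2 are such a subset, unless all groups deploy. With about 12 clusters, chance alone can give that subset a lopsided split.

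Two things are at stake for a primary hypothesis. First, precision: the variance of the arm difference depends on the number of deployed clusters in each arm. Second, comparability: with a handful of deployed clusters, arm may line up by chance with a particular rotation or deployment period. A deployment-history covariate cannot supply a cluster that one arm lacks, and it can do little to separate arm from rotation when each arm has only two or three clusters.

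**Working it through.** **Inputs.** From the article: 12 clusters of 50 (section 2.7.1), equal allocation so about 6 per arm (section 2.4), random blocks of 4, 6 and 8 (section 2.2.1), two-sided 0.05 (section 2.7). Assumed: k of the 12 groups deploy, each as a whole, and cluster sizes are equal. The article gives no k, so it is ranged.

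**The plan's own figure.** Section 2.7.1 states at least 80% power at d = 0.30. With 6:6 clusters of 50 and an intracluster correlation (ICC) of 0, the standard error is √[(1/50)(1/6 + 1/6)] = 0.0816, the ratio is 0.30/0.0816 = 3.67, and power is Φ(3.67 − 1.96) = 95.7% (91.1% with a t test on 10 df). No ICC is stated, so the figure cannot be uniquely reproduced. It is true for ICC up to about 0.0147 (normal) or 0.0081 (t).

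**Split of the deploying groups at an overall 6:6.** The probability that a of k fall in a given arm is C(6,a)·C(6,k−a)/C(12,k). The two mirror-image splits are added.

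| k | Even split | Uneven splits |
|---|---|---|
| 2 | 1:1 54.5% | 2:0 45.5% |
| 3 | (2:1 81.8%) | 3:0 18.2% |
| 4 | 2:2 225/495 = 45.5% | 3:1 240/495 = 48.5%; 4:0 30/495 = 6.1% |
| 6 | 3:3 400/924 = 43.3% | 4:2 450/924 = 48.7%; 5:1 72/924 = 7.8%; 6:0 2/924 = 0.2% |
| 8 | 4:4 45.5% | 5:3 48.5%; 6:2 6.1% |

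**The stated blocks, simulated** (40,000 lists, the three block sizes taken as equally likely). Because the last block may be cut off, 12 groups split exactly 6:6 in 73.6% of lists.

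- Deploying groups at random places: k = 4 gives 2:2 in 44.9%, so 3:1 or worse in 55.1%. k = 6 gives 3:3 in 41.9%, so 4:2 or worse in 58.1%.
- Deploying groups first on the list, where the blocks help: k = 4 gives 3:1 in 28.8% and 4:0 in 1.0%, together 29.8%. k = 6 gives 4:2 in 27.4%.

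**Cost of a split.** Efficiency relative to an even split is 4ab/(a+b)²:

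- 3:1: 12/16 = 0.75, a loss of 25%
- 4:2: 32/36 = 0.89, a loss of 11%
- 5:3: 60/64 = 0.94, a loss of about 6%

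**In power terms,** at d = 0.30 and an assumed ICC of 0.01 (design effect 1 + 49 × 0.01 = 1.49), normal / t test:

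- 6:6: 85% / 77%
- 3:3: 57% / 37%; 4:2: 52% / 34%
- 2:2: 41% / 18%; 3:1: 33% / 15%

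Going from 12 clusters to 6 costs more than the split among those 6. Even at ICC 0, a 3:3 deployed subsample has 74% / 51% power, so section 2.7.1's extension of its power to deployment subsamples does not hold for a subsample of that size.

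**What a remedy achieves** (simulated within a scheduled-to-deploy stratum):

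- Keeping blocks of 4, 6 and 8: 3:1 in about 28% and 4:0 in about 1% (k = 4); 4:2 in about 28% (k = 6).
- Blocks of 2 and 4: 2:2 in about 91% (k = 4), 3:3 in about 87% (k = 6).
- Blocks of 2: always even, or within one group when k is odd.
- Constrained draw: of the C(12,6) = 924 possible 6:6 allocations, C(4,2)·C(8,4) = 6 × 70 = 420 split four deploying groups 2:2, and C(6,3)·C(6,3) = 400 split six 3:3. Ample allocations remain for a random draw.

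**The case against.** The strongest objection is that the premises are not in the documents. Nothing says how many groups will deploy, that a randomized group deploys together, or that schedules are known at randomization. Section 2.3.1 suggests that many may deploy: recruitment starts in a brigade that deploys regularly, and back-up units are chosen to resemble it. Section 2.7.2 dates deployment per participant, so deployers may be spread within groups. All of this stands, and it makes the size of the problem conditional.

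A reader might infer that few groups will deploy and that they could easily all land in one arm, leaving hypothesis 2 untestable. The documents do not support that. Under a 6:6 split, such an outcome has a chance of 45% with 2 deploying groups and 18% with 3, but 6% with 4 and 0.2% with 6, and it is impossible from 7 upward.

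A second objection is that section 2.4 describes randomization of participants, under which deployers would tend to balance over hundreds of people. That wording conflicts with section 2.2.1 and with the cluster power calculation in section 2.7.1. Two of the three places describe clusters, so the point stands for the design as sized, but the conflict needs resolving.

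Third, chance imbalance occurs in any trial with 12 clusters and is not bias. That is true. Here, though, it falls on a subset that carries a primary hypothesis, and part of it can be avoided before allocation.

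**Conclusion.** The point holds in conditional form. As described, the allocation does nothing to balance the clusters on which primary hypothesis 2 rests. If deployment follows the groups and 4 or 6 of 12 deploy, an uneven split is somewhat more likely than not (about 55–58%), or has a chance of about 27–30% if those groups come first on the list. The loss is moderate: a quarter of the efficiency at 3:1 and about a ninth at 4:2. It is small if 8 deploy (about 6% at 5:3) and smaller still if deployment is spread within groups. All deploying groups falling in one arm is a material risk only if 2 or 3 deploy.

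These figures assume 12 equal clusters, whole-group deployment and, for the power figures, an ICC of 0.01. The change is worth making because it is cheap and concerns a primary hypothesis. The present scheme does not invalidate the trial.

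**What to change.** For groups not yet randomized, ask unit leadership before allocation whether the group is scheduled to deploy within the 16-month follow-up. Allocation already precedes recruitment, and section 2.8 already has the team coordinating the training calendar with leadership. Where the answer is known, do one of the following:

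- stratify on it with small blocks (2, or 2 and 4), since the present block sizes within the stratum would leave most of the imbalance in place; or
- if the groups are known up front, draw at random from the 6:6 allocations that split the scheduled-to-deploy groups as evenly as possible.

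At the same time, reconcile section 2.2.1 with section 2.4: state whether groups or participants are randomized, and at which level rank is used.

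The cost is one question to leadership and a new list for the remaining groups. Allocation within small strata is easier to predict, most of all with blocks of 2. Schedules may change, in which case the balance achieved is on planned deployment and only partly on actual deployment. The change does not restore the power lost because fewer clusters deploy.
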